## Abstract

**Introduction:** During the COVID-19 pandemic, confinement measures are likely to produce collateral damage to health (stress, confusion, anxiety), especially in frail individuals and those living with cardiovascular disease (CVD). In cardiac patients in particular, these measures dramatically increase the level of physical inactivity and sedentary lifestyle, which can decrease cardiorespiratory capacity and increase the risk of acute events, rehospitalization, and depressive syndromes. Maintaining a minimum level of physical activity and cognitive stimulation during the COVID-19 crisis is essential for cardiac patients. This study is designed to document the effects of 6 months of home-based physical exercise alone or combined with cognitive training on cognitive and physical functions in patients with CVD over 50 years old.

**Methods and Analysis:** 122 patients (>50 years old) with stable CVD and no contraindication to perform physical exercise training will be recruited and randomly assigned to one of the 2 following arms: (1) Home-based physical exercise alone, (2) Home-based physical exercise combined with cognitive training. The intervention lasts 6 months, with remote assessments performed prior to, mid and post-training. A follow-up 6 months after the end of the intervention (12 month) is also proposed. The primary outcome is cognition, including general functioning (Montreal Cognitive Assessment (MoCA) score), as well as performances on measures of executive functions, processing speed, and episodic memory. The secondary outcome is physical performance, including balance, gait and mobility, leg muscle strength and estimated cardiorespiratory fitness. Tertiary outcomes include mood, anxiety, and health-related quality of life as assessed by self-reported online questionnaires.

**Discussion:** With the COVID-19 crisis, there is a critical need for remote exercise and cognitive training, and to further investigate this topic, in particular for cardiac patients. The present context can be viewed as an opportunity to perform a major shift from center-based programs to home-based physical exercise. This is especially important to reach out to older adults living in remote areas, where access to such interventions is limited.

**ClinicalTrials.gov:** [https://clinicaltrials.gov/ct2/show/NCT04661189], NCT04661189.

## Introduction

Because of the COVID-19 pandemic, the population has been forced to home confinement since spring 2020, drastically reducing social interactions and altering physical activity and eating behaviors (1). This sudden lockdown radically changed the population's lifestyle (gym services are also closed), with activities mainly limited to essential needs (e.g., grocery, pharmacy, or physician visits). This confinement may also have collateral effects on cognitive and physical health (2), especially in individuals at high risk of cognitive decline like older adults (3) and patients with cardiovascular diseases (CVD) (4). Hospitals and clinics must reorganize their care services, while limiting contact between individuals. Ambulatory visits and non-essential services have been reduced, like center-based cardiac rehabilitation programs (CR) stopped or delayed, despite the fact that they are a class I level A recommendation with clinical benefits that are now well documented (5, 6). Thus, effective solutions are needed to enhance cardiovascular health and cognition in patients with CVD, while maintaining social distancing during this pandemic period. Furthermore, the pandemic context will likely persist, and full participation in center-based CR or usual exercise habits might take time or be postponed. Maintaining a minimum of physical activity during the COVID-19 crisis is essential for cardiac patients, with the advice of the medical team who could prescribe remote home-based exercise training (6, 7). Remote supervision of exercise is effective on health outcomes and safe in patients with stable CVD (6, 8–10). It is now well established that physical activity positively impacts health outcomes and cognition in older adults with CVD (11, 12). Cognitive training also enhances cognitive performances in older adults (13) and in cardiac patients post-surgery (14). Moreover, cognitive training and exercise could have a synergistic effect on cognition in healthy older adults compared to exercise training alone (15, 16). However, this synergistic effect has never been investigated in older adults with CVD. Furthermore, while there is increasing interest for multidomain interventions combining cognitive and exercise training to improve cognition in older adults, there is still a lack of knowledge on how much benefits can be gained by adding cognitive training to physical exercise, and regarding the optimal dose of each type of intervention. The COVID-19 crisis has put forward the relevance of home-based training. The present context can be viewed as an opportunity to promote a major shift in remote non-pharmacological interventional programs, so that a larger number of individuals could benefit from them.

The COVEPICARDIO project will investigate the effects of home-based physical exercise with or without cognitive training, on cognitive and physical functions in older women and men with stable CVD.

Hypotheses: 1/ After 6 months of home-based physical exercise, cardiac patients will show an improvement in cognitive (primary outcome) and physical measures (secondary outcomes), with larger gains in executive functions. 2/ Cardiac patients randomized in the combined home-based physical exercise and cognitive training group will show greater improvements in cognition and physical functions post-intervention compared to cardiac patients who did not complete the cognitive training.

## Methods and Analysis

### Study Design

The COVEPICARDIO study will be a prospective, single-blind, randomized trial with two parallel intervention arms (1:1): 1/ Physical exercise: remote monitoring and coaching of home-based physical exercise, 2/ Physical exercise, and cognitive training: remote monitoring and coaching of home-based physical exercise and cognitive training. The intervention will last 6 months. Three testing periods lasting 7 to 10 days each will be performed remotely at baseline, three (mid-training) and 6 months (post-training), using videoconference supervision and online questionnaires. Six months after the end of the intervention (12 months), a follow-up assessment will also be performed to explore the potential retention of intervention effects. Since this follow-up does not directly address the main hypotheses, participation will be optional.

### Participants

A total of 122 participants with stable CVD will be included.

#### Inclusion Criteria

Participants will be adults aged 50 and older who have access to Wi-Fi connected to the internet and possess a tablet (e.g., iPad or Android) or a computer. Individuals will be included if they have stable coronary artery disease, stable chronic heart failure, corrected valvular heart disease, or atrial fibrillation, with a low-risk profile, as determined by the physician, and with no contraindication to exercise training.

#### Exclusion Criteria

1/ Non-cardiopulmonary limitation to exercise (e.g., severe arthritis) or a severe exercise intolerance. 2/ Severe respiratory disease (e.g., COPD, severe COVID-19 related symptoms, severe asthma). 3/ Significant cognitive impairment (i.e., score of 18/23 or lower on the telephone version of Mini-Mental State Examination, MMSE) (17). 4/ Contraindications to exercise testing/training (18) (e.g., uncorrected severe aortic stenosis, severe pulmonary hypertension, severe non-revascularizable coronary disease including left main coronary stenosis, significant myocardial ischemia or arrhythmia during low-intensity exercise).

### Interventional Methods

All assessments, exercise monitoring, and cognitive training will be performed remotely. Patients will be identified and recruited by Montreal Heart Institute's (MHI) physicians. During a pre-screening phone call, individuals will be asked about their interest in taking part in the study and whether they possess the proper setup to access the online tools. After a short medical questionnaire, an appointment will be fixed for a preliminary session; they will receive the information and consent form by email prior to this session. During the preliminary session, a staff member will provide details about the consent form. Participants will then be given the opportunity to provide oral consent. They will then be asked to send a written consent by email. If an oral consent is obtained, the cognitive [the telephone version of the Mini Mental State Examination; MMSE (19)] and physical (Physical Activity Readiness Questionnaire; PARQ+) screenings will be performed with a research assistant and will later be reviewed by a neuropsychologist and a kinesiologist, respectively. Once the research team receives the written consent by email and ensures eligibility, the participant will be considered enrolled. A technology tutorial will then be scheduled to ensure that internet access and tools are ready and sufficiently mastered by participants prior to the remote assessments. After baseline assessment, participants will be randomized into one of the two arms. Participants will receive automatic standardized communications by email to transmit study information like appointment scheduling, links to self-reported online questionnaires, and training guidelines. An online platform will centralize all the follow-up information. Staff members will have distinct access to either assessment or training information according to their role, to preserve the study blinding. A non-overwriting process will ensure data integrity: all form submissions will be recorded in a journal fashion.

#### Exercise and Cognitive Intervention

Participants will receive a group-specific training guide according to their randomization. This training guide contains only recommendations about the nature, intensity, and frequency of training sessions. Participants will then attend an introductory session over the phone given by their training coach.

##### Exercise Monitoring

Participants will be encouraged to complete a home-based physical exercise using video capsules available via Facebook or Youtube, created by the Centre EPIC of the MHI's team of kinesiologists (20). Aerobic, muscular strengthening, flexibility, and/or balance exercises are proposed in these videos, and do not require any equipment. Each video lasts ~15 min and includes a 5-min warm-up, followed by a 10-min training, and finally by a 2-min cool-down period. Guidelines are provided by kinesiologists to allow participants to adapt the exercise to their physical capacities. Participants will be invited to perform exercise sessions at least 5 times a week. The exercise sessions can be performed at home using the video capsules, or with other video or web-based training programs. Participants can also engage in outdoor activities (e.g., walking or cycling). To track their adherence, the duration, intensity, and nature of the activity of each training session will be reported by the participant in a journal, that they will transmit to their training coach during their weekly follow-up call. The Borg Rating of Perceived Exertion (RPE) graduated from 0 to 10 will be used by participants to assess the intensity of their exercise sessions.

##### Cognitive Training

The combined intervention will include home-based cognitive training in addition to physical exercise as described in the previous section. Participants will be asked to complete their home-based cognitive training prior to exercise training or at least 3 h post-exercise session (21). Participants will also be asked to perform their cognitive training in a comfortable position, while limiting distraction. Validated computerized cognitive training tasks, as well as video capsules will be provided. Participants will be encouraged to complete a minimum of 3 sessions per week (15–20 min/session, maximum 1 session/day), i.e., two computerized cognitive training sessions and one video capsule session. Three tasks will be available during the computerized cognitive training sessions: 1/ dual-task training, during which participants must maintain and prepare for several response alternatives and must share attention between two concurrent tasks (i.e., Dual-task), 2/ inhibition training, during which participants must refrain from giving an automatic response (i.e., Stroop task), as well as 3/ working memory training, in which participants must maintain and update information in working memory to recall items presented earlier (i.e., N-Back task). Each cognitive task lasts approximately 15 min and comprises its own sets of visual stimuli (e.g., letters, numbers, symbols) and matching button symbols. Participants will be asked to perform the tasks as fast as possible while maintaining accuracy. The three tasks will be presented in a fixed order for all participants. Task difficulty will increase gradually over the course of the participant's cognitive training to avoid task automatization and to maintain stimulation (22). Live visual feedback will be provided during training, as well as a histogram of daily performances to encourage improvement. Once per week, participants will be asked to complete a strategy-based training, via video capsules. This training is an adapted version of the MEMO+ program, which has been validated previously (23). Participants will learn different mnemotechnics (e.g., face-name association, visual imaging), and will learn about age-related changes in memory. In addition, some video capsules are targeted to help participants develop strategies to cope with multiple aspects of their daily life, such as sleep, anxiety, and nutrition. To track cognitive training adherence, participants will be asked to complete a follow-up agenda and to indicate days and times when they completed cognitive training sessions. Training adherence for computerized cognitive training tasks will also be monitored online.

#### Remote Monitoring and Coaching

Once a week, kinesiologists will call participants to (1) motivate them to stay engaged in their training, (2) ensure the safety of the exercise training sessions, and (3) to collect exercise and cognitive training data reported by participants in their follow-up agenda during the previous week. The kinesiologists will also provide updated information about training resources available online, track participant's adherence, and advise participants according to their training characteristics and study training guidelines.

#### Measurements and Outcomes

Participants will complete videoconference assessments prior to the intervention, mid-intervention (3 months), post-intervention (6 months), as well as 6 months following the end of the intervention (12-month follow-up). All the testing procedures are reported in Figure 1. At baseline, demographics, and medical information, including chronic diseases, comorbidities, and medications will be collected by medical questionnaire. A COVID-19 questionnaire (i.e., QCOVID) will address the social and financial consequences of the COVID-19 pandemic on participants, as well as its impact on their physical activity routines.

**Figure 1 F1:**
[figure not shown]
Schedule of enrolment, interventions, and assessments according to SPIRIT guidelines. ^1^Montreal Cognitive Assessment, Trail Making Test, Verbal Fluency Test, Digit Span Test, Similarity Test, Rey Auditory Verbal Learning Test. ^2^One leg balance test, 5-time Sit to Stand test, Timed up and go test, 4-meter walking speed test. ^3^Matthew questionnaire for estimated cardiorespiratory fitness, SF-12, Pittsburgh Sleep Quality Index and Berlin Questionnaire, Short Diet Questionnaire, Stait Trait Anxiety Inventory, Geriatric Depression Scale, Perceived Stress Scale, Perseverative Thinking Questionnaire, Intolerance of Uncertainty Scale, Connor Davidson Resilience Scale 10, Anxiety Sensitivity Index, Social and Community Involvement Questionnaire, Lubben Social Network Scale. The following questionnaires will be completed at baseline only: Medical questionnaire, Q-COVID questionnaire, Physical Activity Scale for the Elderly, Cognitive Reserve Questionnaire, Bem sex-role Inventory.

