##### Tertiary Outcomes

The following tertiary outcomes will be measured with validated self-reported questionnaires that participants will fill in through online forms: **1/ Sleep:** Participants will complete the Pittsburgh Sleep Quality Index (PSQI) and the Berlin Questionnaire. PSQI scores range from 0 to 21, a lower score indicating better sleep quality. The Berlin Questionnaire will determine the risk of sleep apnea. **2/ Anxiety/mood:** The Geriatric Depression Scale (GDS), the Perceived Stress Scale, the SF-12 (quality of life), the State-Trait Anxiety Inventory, the Anxiety Sensitivity Index, the Intolerance of Uncertainty scale, the Perceived vulnerability to disease, the Connor-Davidson Resilience Scale 10, and the Perseverative Thinking Questionnaire, will be used to assess mood and anxiety. **3/ Cognitive reserve:** will be evaluated at baseline. To do so, participants will provide their total years of education and will complete a modified version of the Rami and colleague's cognitive reserve questionnaire (33), adapted for French and English by the CIMA-Q team (17, 34). **4/ Social support:** Social and Community Involvement Questionnaire (35) and the Lubben Social Network Scale will be completed. **5/ Diet:** Participants will complete the Short Diet Questionnaire (36). **6/ Prior physical activity:** Participants will fill in the Physical Activity Scale for the Elderly (37). **7/ COVID-19 impact:** The QCOVID questionnaire will be completed at baseline only. **8/ Gender:** The Bem Sex-Role Inventory will be filled at baseline only. All questionnaires will be filled in by participants using anonymous online forms.

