This trial proposes crisis-adapted lifestyle interventions and remote assessments. More precisely, to further ensure the continuity and the regularity of the exercise training, the proposed trial offers weekly phone call support and an online video training program, providing a wide range of exercises to help participants maintain their exercise routine even during the lockdown. In CVD, among the patients who complete a phase II center-based CR about half of the patients tend to return to their previous lifestyle habits, become sedentary again after a few months, and are non-adherent to physical activity target levels recommended by physicians (40, 41). Home environment with regular contact with telephone support or videoconference from the medical or research team may be more likely to help sustain positive physical and psychosocial changes over time, compared to institution-based programs (42–44).

Most participants in exercise clinical trials come from urban areas, which likely limits generalization of findings, and individuals from rural communities are still underrepresented (45). Home-based interventions, made available for all, would address this problem, and offer a great solution to counteract sedentary/inactivity behavior in the COVID-19 pandemic situation. A home-based combined intervention with exercise and cognitive training could help to maintain and enhance cognition and cardiovascular health in older adults with CVD who could no longer access training facilities during the COVID-19 lockdown.

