Secondly, our participants do not have precise control of the intensity and duration of the exercise sessions (heart rate monitors, pedometers, or other tools). This is only declarative data reported weekly with the kinesiologists. Our study focuses on exercise and cognitive training in CR's phase III and should not be confused with a comprehensive CR program delivered in phase II. Adherence to medication, diet and appropriate teaching about patient's risk factors and CVD are critical aspects of a comprehensive CR program (phase II). Consequently, we will include some patients who have completed a CR program and others who have not benefited from this program. Then, non-exercise prediction of cardiorespiratory fitness with an equation is valid for healthy individuals, but little is known about its reliability in patients with CVD. Moreover, variability was observed in the accuracy between non-exercise prediction equations and the ability of equations to detect changes in cardiorespiratory fitness (46). Therefore, the use of non-exercise prediction equations could lead to a significant error in the estimated change of participants' cardiorespiratory fitness. Finally, sex was not taken into account in recruitment and randomization processes, although sex differences have been reported on cognition (47), as well as in exercise-training effects on cognition in healthy older adults (48). No study to date has documented potential sex-related differences with regards to the effects of exercise, cognitive or combined training on cognition and physical outcomes in older adults with CVD. Given the sex-related differences in cognition, exercise intervention effects and diseases, sex differences are to be expected in the present study.

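### No dedicated activity measure is taken on one scale before and during the programme, so the dose-response analysis cannot separate habitual from new exercise

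*Protocol article*

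**What the plan says.** Before the intervention, the article's dedicated activity measure is the PASE. Tertiary Outcomes lists it under prior physical activity ("Participants will fill in the Physical Activity Scale for the Elderly"), and the Figure 1 caption restricts it to one visit: "The following questionnaires will be completed at baseline only: Medical questionnaire, Q-COVID questionnaire, Physical Activity Scale for the Elderly, Cognitive Reserve Questionnaire".

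During the intervention, activity is self-reported session by session. Exercise Monitoring says that "the duration, intensity, and nature of the activity of each training session will be reported by the participant in a journal", and Remote Monitoring and Coaching has the kinesiologist collect these entries in a weekly call. The frequency is an invitation: "Participants will be invited to perform exercise sessions at least 5 times a week". The content is open: "The exercise sessions can be performed at home using the video capsules, or with other video or web-based training programs", and "Participants can also engage in outdoor activities (e.g., walking or cycling".

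Study Limitations turns the journal into a weekly dose in kcal and METs, averages it over the six months, and may split participants into terciles. It presents this analysis as a partial answer to the absence of a group without intervention. The same section says of prior rehabilitation that "we will include some patients who have completed a CR program and others who have not benefited from this program".

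Hypothesis 1 predicts improvement after six months of home-based exercise. Statistical Analysis treats a significant pre-post difference as evidence of efficacy and calls this the primary hypothesis.

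**The concern.** The baseline measure is not repeated, and the measure taken during the trial has no baseline. They are on different scales, so one cannot be subtracted from the other.

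Two readings suffer:

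- **The dose-response analysis.** It supports the exercise programme only if a higher dose means more exercise because of the programme. A raw level also reflects how active the patient was beforehand. Long-standing exercisers may differ in cognition and fitness for reasons unrelated to the trial.
- **The pre-post result for hypothesis 1.** If cognition does not change, a reader will want to know whether exercise failed to help or whether patients exercised no more than before. The planned data answer that poorly.

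A rise in activity cannot be taken for granted. The programme is advisory, eligibility sets no upper limit on current activity, and some entrants have already been through rehabilitation.

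**Working it through.** The plan gives no figure on this point, so the first check sets the instruments side by side.

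| Source of activity data | Before the programme | During the programme | Scale |
|---|---|---|---|
| PASE (Tertiary Outcomes; Figure 1 caption) | yes | no | PASE score |
| Session journal (Exercise Monitoring; Study Limitations) | none described | yes, weekly | kcal and METs |
| Q-COVID (Measurements and Outcomes; Figure 1 caption) | yes, effect of the pandemic on routines | no | questionnaire |
| Activity item in the Matthews questionnaire (Secondary Outcome; Figure 1 caption) | yes | apparently yes | input to a VO2max prediction |

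**Step 1: which before-after differences exist.**
- Journal during minus journal before: the second term is not collected.
- PASE during minus PASE before: the first term is not collected.
- Journal minus PASE: the units differ.
- Matthews item: it is in the questionnaire battery and not on the baseline-only list, so a difference appears possible. The schedule figure is not shown, so repetition is inferred from the caption.

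**Step 2: what the dose contains.** Write the logged weekly dose as L = H + N, where H is activity the patient already did and now logs, and N is activity added because of the programme. The plan analyses L. Without a baseline on the same scale, H is unknown and N cannot be recovered.

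**Step 3: illustration.** Assume that a patient already walks five times a week for 30 minutes, changes nothing and logs the walks. A second patient was inactive and now follows five study videos.
- Walker: L = 5 × 30 = 150 min/week, N = 0.
- New exerciser: L = 5 × 15 = 75 min/week, N = 75. Adding the stated parts of a video (5 + 10 + 2 = 17 min) gives 5 × 17 = 85.

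The order depends on the assumed walk length:

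| Assumed walk | Walker's L (N = 0) | Against 75 to 85 for the new exerciser |
|---|---|---|
| 10 min | 50 | lower |
| 15 min | 75 | equal to lower |
| 20 min | 100 | higher |
| 30 min | 150 | higher |

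The planned dose also weights by intensity. With 30-minute walks the walker still ranks higher unless the videos carry more than 150/75 = 2 times the MET value of the walk (150/85 = 1.76 with 17-minute videos). A reversal is therefore possible. Nothing in the article says how often it would occur.

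**Step 4: the between-arm comparison.** Under Cognitive Training, the combined arm receives the same exercise component plus cognitive training. Randomisation balances H between arms in expectation. The sample size of 49 per arm rests on the between-arm difference of 0.425 − 0.239 = 0.186 and does not use any activity measure.

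**The case against.** A reader might infer that the trial cannot show any change in activity. The documents do not support that. The Matthews questionnaire asks for self-reported activity and appears to be repeated, so some before-after information on one scale should exist. Study Limitations doubts the predicted change in fitness, not the activity answer itself. That answer is still a weak substitute: the article uses it only as an input to a fitness prediction, so using it as the exposure would tie exposure to a secondary outcome.

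A reader might also infer that habitual activity officially counts as the intervention, or that an unchanged walker would be classed as fully adherent. The article says neither. It allows walking and cycling, logs training sessions and gives no adherence threshold. The training guide, which is not shown, may say how sessions are credited. What stands is that nothing described distinguishes old from new activity.

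The Discussion says of rehabilitation completers that "about half of the patients tend to return to their previous lifestyle habits". It is tempting to conclude that the other half enter the trial already active. The figure is not an activity rate for this sample, the share of completers is unknown, and the Discussion also describes cardiac patients as tending to be inactive.

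Further, hypothesis 1 is worded as improvement after exercise, not as a rise over earlier activity. The larger attribution problem is the missing untreated arm, which the authors disclose. A repeated activity scale would not cure it, since a rise could also reflect easing confinement. All of this stands and limits the point. It does not remove it: the authors concede the missing control and the self-reported data, but not the missing baseline dose, and they rely on dose as the mitigation.

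**Conclusion.** The point holds in a limited form. The stated schedule leaves no dedicated activity measure on one scale both before and during the programme. The dose-response analysis as described cannot separate habitual from programme-induced exercise, and a rise in activity can be shown only weakly.

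The size of the distortion cannot be computed, because the article gives no distribution of prior activity. The 150 against 75 min/week contrast rests on assumed walks and shows only that the ranking can reverse.

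The consequence is confined to the dose-response analysis and to the interpretation of the pre-post result. The randomised comparison and its sample size are largely unaffected. This is a worthwhile, low-cost improvement and not a flaw in the trial's main contrast. The conclusion assumes that no journal is kept before randomisation, since none is described, and that the Matthews questionnaire is repeated as the caption suggests.

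**What to change.** 1. Repeat the PASE in the existing online battery at T1 (3 months) and T2 (6 months).
2. Report within-person change in PASE by arm, as context for the pre-post result.
3. In the dose-response analysis, use change in PASE alongside the journal dose, and adjust the journal dose for baseline PASE. The adjustment needs no new data collection and works although the scales differ.
4. For participants not yet enrolled, a journal week before randomisation is optional. It would give a baseline dose in kcal and METs. However, a week inside the 7 to 10 days of testing may not be typical, and participants already enrolled would lack it.
5. State that a documented rise in activity does not replace an untreated control.

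The hypothesis 1 claim should not be made conditional on activity having risen. That would hang the primary claim on a self-reported, post-baseline variable with no set threshold.

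The cost is a few minutes of participant time at two visits. The measure remains self-reported, and participants who have already passed T1 or T2 will lack that repeat, so their number should be reported. Intervention, eligibility and sample size do not change.
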